The enrolment period will last from June to December 2013. Each subject will be requested to compile a structured questionnaire at the time of enrolment at after 6, 12, 24, 36 and 60 months (and eventually, in the case of an expansion of the follow-up, at 84 and 120 months). After the first contact, the follow-up questionnaires will be compiled through a phone interview or through a specifically created website (http://www.ipazienti/fumo), with private password. To reduce potential misclassification, the level of carbon monoxide in expired after breath will be evaluated in all subjects declaring no traditional cigarette smoking in any phase of the follow-up, using portable carbon monoxide analyzers (Smokerlyzer ® piCO + ™, Bedfont Scientific Ltd.). Such an assessment will be made by the investigators, after specific periodical calibration, directly at the home of the participant or at the office of his/her general practitioner. Among the methods to monitor self-reported smoking cessation, also the assessment of cotinine in saliva can be made using portable and relatively economical devices, and such test showed a slightly higher sensitivity/specificity than tests based upon exhaled CO [27]. However, we were not able to find a seller of cotinine portable tests on saliva, and the measurement of breath CO still showed high levels of sensitivity (>90% [27,28]).

Each participant will have to sign a written informed consent. The study protocol has been registered in Clinicaltrials.gov (NCT01785537) and approved by the Ethics Committee of the University of Chieti (Record n. 6; 25-03-2013).

Participants will be enrolled at various study sites within the Abruzzo and Lazio Region using the same standardized procedures.

All the subjects that will be excluded because of past episodes of selected smoking-related major diseases will be requested to participate into a nested case–control pilot study, in which we will collect hospital admission data retrospectively and compare the rates of smoking-related diseases according to the present and past smoking habits.

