### Interventions and groups

This is a non-interventional observational study. The participants will be divided into three cohorts/groups according to their self-determined smoking pattern:

– Group EC - smokers of e-cigarettes only (who are not smoking traditional cigarettes). This group will be further split in the analysis: never or former smokers of traditional cigarettes; smokers of e-cigarettes with or without nicotine.

– Group TC - smokers of traditional cigarettes only. This group will be further split in the analysis: recent and older smokers.

– Mixed Group - smokers of both traditional and electronic cigarettes. This group will be further split in the analysis: mixed smokers who quit and who did not quit traditional cigarette smoking during follow-up.

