### Secondary outcomes

1. Adherence to e-cigarette smoking: number of months of continued e-cigarette smoking in groups EC and Mixed.

2. Traditional and electronic smoking (overall smoking) cessation: percentage of subjects in all groups reporting sustained smoking abstinence from both traditional and electronic cigarette smoking at 6, 12, 24, 36 and 60 months. Smoking abstinence is defined as complete abstinence from tobacco or electronic smoking (not even a puff) for the 30 days period prior to the visit.

3. Time to hospital admission for one of the followings: cardiovascular diseases, chronic obstructive pulmonary diseases, cancer of the lung, esophagus, larynx, oral cavity, bladder, pancreas, kidney, stomach, cervix, and myeloid leukemia. Repeated admissions of the same subject will be counted once and the subject will be censored at the date of the first admission.

4. Rate of subjects with smoking-related hospitalizations: percentage at 1, 2, 3 and 5 years of subjects who had a hospital admission for one of the followings: cardiovascular diseases, chronic obstructive pulmonary diseases, cancer of the lung, esophagus, larynx, oral cavity, bladder, pancreas, kidney, stomach, cervix, and myeloid leukemia. Repeated admissions of the same subject will be counted once.

5. Number of smoking-related hospitalizations: mean number at 1, 2, 3 and 5 years of hospital admissions for one of the followings: cardiovascular diseases, chronic obstructive pulmonary diseases, cancer of the lung, esophagus, larynx, oral cavity, bladder, pancreas, kidney, stomach, cervix, and myeloid leukemia. Each admissions of the same subject will be counted.

6. Number of hospitalizations for cardiovascular diseases: mean number at 3 and 5 years of hospital admissions for cardiovascular diseases. Each admissions of the same subject will be counted.

7. Number of hospitalizations for smoking-related cancers: mean number at 3 and 5 years of hospital admissions for cancer of the lung, esophagus, larynx, oral cavity, bladder, pancreas, kidney, stomach, cervix, and myeloid leukemia. Each admissions of the same subject will be counted.

8. Self-reported quality of life: average quality of life according to EuroQoL EQ-5DL at 6, 12, 24 and 36 months. The analysis of quality of life will follow the technical specifications recommended by the EuroQol group [29].

9. Reported side effects at 6, 12, 24, 36 and 60 months.

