All outcomes will be self-reported; primary outcome 1 and secondary outcome 2 will be checked using portable CO analyzers, and secondary outcomes 3–7 will be checked using hospital discharge abstracts through a linkage to fiscal codes (for the residents in Abruzzo only). The permission will be granted from each participants and hospitalization data will be provided by the Regional Healthcare Agency of Abruzzo. The admissions for each of the conditions included in the composite outcomes will be defined as follows, based upon the ICD-9-CM principal diagnosis codes in the Italian hospital discharge abstracts (SDO):

– COPD or asthma - 490, 490.0, 491.1, 491.2, 491.21, 491.8, 491.9, 492.0, 492.8, 494, 494.0, 494.1, 496, 493.00, 493.01, 493.02, 493.10, 493.11, 493.12, 493.20, 493.21, 493.22, 493.81, 493.82, 493.90, 493.91, 493.92 [30]

– Myocardial infarction - 410.0-410.9

– Congestive heart failure - 428.0-428.9

– Transitory cerebrovascular ischemia - 435.0-435.9

– Stroke - 433.0-434.9

– Cancer of the lung - 162.0-162.9

– Cancer of the esophagus - 150.0-150.9

– Cancer of the larynx - 161.0-161.9

– Cancer of the oral cavity - 140.0-149.9

– Cancer of the bladder - 188.0-188.9

– Cancer of the pancreas - 157.0-157.9

– Cancer of the kidney - 189.0

– Cancer of the, stomach - 151.0-151.9

– Cancer of the cervix - 180.0-180.9

– Myeloid leukemia - 205.0-205.9

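### Breath CO can check only the tobacco half of secondary outcome 2, so concealed e-cigarette use goes unchecked and the overall-cessation comparison can tilt towards e-cigarette users

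*Protocol article*

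**What the plan says.** Under Secondary outcomes, the second outcome is the "percentage of subjects in all groups reporting sustained smoking abstinence from both traditional and electronic cigarette smoking at 6, 12, 24, 36 and 60 months". Abstinence is defined there as "complete abstinence from tobacco or electronic smoking (not even a puff) for the 30 days period prior to the visit".

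The paragraph that follows the list says that all outcomes are self-reported and then that "primary outcome 1 and secondary outcome 2 will be checked using portable CO analyzers". That clause does not limit the check to one component. The same sentence does limit the hospital-record linkage, to residents of Abruzzo.

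Study design and population describes the test itself. Breath CO is "evaluated in all subjects declaring no traditional cigarette smoking in any phase of the follow-up", with the aim of reducing misclassification. Its sensitivity is given as above 90%, in a discussion of ways to monitor self-reported smoking cessation. Salivary cotinine was considered and set aside: "we were not able to find a seller of cotinine portable tests on saliva". No check of e-cigarette use is described.

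Interventions and groups defines EC as people who use e-cigarettes and do not smoke traditional cigarettes, some with nicotine and some without. Primary outcome 1 includes the former smokers in that group.

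**The concern.** One test is assigned to two outcomes that ask different things of it. For primary outcome 1, a person who uses e-cigarettes and does not smoke must pass. For secondary outcome 2, the same person must count as a failure. A test that such a person passes cannot show that e-cigarette use has stopped.

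The gap is uneven across groups. A TC participant who keeps smoking and claims to have stopped everything will usually be found out. An EC participant who keeps using e-cigarettes and makes the same claim will not. Overall cessation would thus be corrected for concealed use of the baseline product in one group and left uncorrected in the other, under a sentence that presents the outcome as checked. The article wants its results to inform guidelines and regulatory decisions on e-cigarettes, so an apparent cessation advantage arising from unequal checking would matter.

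**Working it through.** **Step 1: what the test can show.** The article does not say whether e-cigarette use raises breath CO, so take both possibilities.

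- If it does not, the test works for primary outcome 1 in EC and in Mixed participants who give up tobacco only, but carries no information on the electronic part of secondary outcome 2.
- If it does, the electronic part could be checked, but primary outcome 1 would fail: EC former smokers who have not returned to tobacco would test positive.

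The article's use of the test for primary outcome 1 relies on the first case. The trigger fits this, since it is a declaration about traditional smoking and not about e-cigarettes.

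**Step 2: which false claims are caught.** Anyone claiming overall abstinence also claims tobacco abstinence and so is tested.

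| What the false claim hides | TC | Mixed | EC |
|---|---|---|---|
| Tobacco smoking | mostly caught | mostly caught | mostly caught |
| E-cigarette use only | missed | missed | missed |

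The rows are alike in every group. The imbalance arises because continuing the baseline product falls in the first row for TC, in the second for EC, and in either for Mixed.

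**Step 3: size.** The article gives no figure on this point to reproduce. Inputs:

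- p, true overall abstinence, equal in TC and EC: assumed, 10% (20% as a variant).
- f, share of non-abstainers who falsely claim abstinence, equal in both groups: assumed, 1% to 10%.
- s, chance that CO exposes concealed smoking: 0.90, from the stated sensitivity of above 90%.
- Further assumptions: false claims concern the baseline product only, a positive reading overturns the claim, and true abstainers pass.

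Formulas:

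- TC observed = p + (1 − p) × f × (1 − s)
- EC observed = p + (1 − p) × f
- Spurious EC advantage = (1 − p) × f × s

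With p = 10% and s = 0.90 the advantage is 0.9 × 0.9 × f = 0.81 × f:

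| f | TC observed | EC observed | Spurious advantage (points) |
|---|---|---|---|
| 1% | 10.09% | 10.9% | 0.81 |
| 3% | 10.27% | 12.7% | 2.43 |
| 5% | 10.45% | 14.5% | 4.05 |
| 10% | 10.9% | 19.0% | 8.1 |

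With p = 20% it is 0.8 × 0.9 × f = 0.72 × f, so 3.6 points at f = 5% and 7.2 at f = 10%.

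**Step 4: how firm the direction is.**

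- *Weaker detection.* One breath reading cannot cover 30 days without a puff. If s were only 0.5, p = 10% and f = 5% would give 0.9 × 0.05 × 0.5 = 2.25 points.
- *Unequal misreporting.* With separate false-claim rates, EC still gains unless its rate is below (1 − s) = one tenth of the TC rate.
- *Claims not about the baseline product.* Let h be the share of TC false claims that hide e-cigarette use only, and r the share of EC false claims that hide tobacco. The advantage becomes (1 − p) × f × s × (1 − h − r). It shrinks as either grows and reverses only if h + r exceeds 1.
- *Mixed.* If a share g of Mixed false claims hides e-cigarette use only, the advantage over TC (taking h = 0) is (1 − p) × f × s × g, between zero and the EC figure.

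**Step 5: would it be noticed?** With 500 per group and 20% dropout, 500 × 0.8 = 400 remain. A two-sided 5% comparison of two proportions (power formula, not Fisher's exact test) would then call the spurious difference significant with probability 41% at p = 10%, f = 5%, and 90% at p = 10%, f = 10%. At p = 20% these are 23% and 66%.

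**The case against.** The strongest reply is that the article never claims overall cessation is verified. The paragraph opens by calling all outcomes self-reported, and the methods tie the CO test to declarations about traditional smoking. Read together, these suggest that CO was meant for the tobacco part, and that the fault is one loose clause about a secondary outcome that neither primary analysis nor the sample size uses. Much of this stands. But the clause as written covers the whole outcome, and even on the kinder reading the unequal checking across groups is not disclosed.

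A reader might infer that the two uses of CO are incompatible. They are not: overall abstinence requires tobacco abstinence, so a positive reading refutes the claim in any group. The check is valid but one-sided and incomplete. A reader might also infer that false claims are caught in TC and missed in EC. That is too absolute: sensitivity is above 90% and not complete, a concealed tobacco relapse in EC can be caught, and a TC participant who switched to e-cigarettes and denies it is missed.

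It is also fair that the size rests on assumed rates. Participants joined EC by declaring e-cigarette use, and nobody is told which product to use, so few may have reason to conceal it. At f = 1% the bias is under one point.

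That cotinine could not be sourced is a reasonable constraint. A nicotine marker would in any case miss users of nicotine-free e-cigarettes.

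**Conclusion.** The concern holds in a limited form. The stated CO check bears on only one of the two components of secondary outcome 2. Concealed e-cigarette use is undetected in every group, and because it is the baseline product in EC and part of it in Mixed, the comparison of overall cessation with TC can be biased towards e-cigarette users.

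The direction is fairly robust under the conditions in step 4 of the working. The size is not known from the article: roughly 1 to 8 points for false-claim rates of 1% to 10%, given equal true abstinence of 10%, equal misreporting and 90% detection. No single value in that range should be read as an estimate of the bias in this study.

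A reader might extend the criticism to primary outcome 1. The article does not support that: that outcome concerns traditional smoking only, which is what the test addresses.

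**What to change.** 1. In the paragraph on outcome checking after the list of secondary outcomes, say that CO checks primary outcome 1 and only the tobacco component of secondary outcome 2, and that e-cigarette abstinence rests on self-report.
2. Report secondary outcome 2 as CO-checked tobacco abstinence and self-reported, unverified e-cigarette abstinence, alongside the composite.
3. Give a misreporting sensitivity range for the EC versus TC and Mixed versus TC contrasts, using the formulas above or an equivalent.

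The cost is a change of wording and one more table, with no new test, visit or participant. The drawback is that secondary outcome 2 is openly shown to be partly unverified, which weakens what can be concluded from it.

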## Methods/design

### Study design and population

This is an observational, prospective cohort study. None of the participants will receive an indication about which product to smoke. In fact, all participants will receive structured flyers reporting the main harms of cigarette smoking.

An individual will be considered for participation if:

– resident in Italy;

– aged between 30 and 75 years;

– smoker of e-cigarettes (inhaling at least 50 puffs per week) since six or more months (EC Group);

– smoker of at least one traditional cigarette per day since six or more months (TC Group);

– smoker of both electronic and traditional cigarettes (at least one per day) since six or more months (Mixed Group).

Exclusion criteria will be:

– illicit drug use,

– breastfeeding or pregnancy,

– major depression or other psychiatric conditions,

– severe allergies,

– active antihypertensive medication,

– angina pectoris,

– past episodes of selected smoking-related major diseases (myocardial infarction, stroke/TIA, congestive heart failure, COPD, cancer of the lung, esophagus, larynx, oral cavity, bladder, pancreas, kidney, stomach, cervix, and myeloid leukemia).

Potentially eligible subjects will be requested participation through newspaper and internet advertisements, through direct contact with an investigator at the shops, finally through direct contact with some of the general practitioners of the Abruzzo Section of the Italian Scientific Society of General Medicine (SIMG) who voluntarily participate to the project. Specific agreements will be established with the sellers to permit the presence of an investigator during conventional working hours. Inclusion and exclusion criteria will be self-reported and further verified by the investigator in case of participation.

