### Timetable, participating units and funding

We will start in June, 2013, and the enrolment period will end in December 31, 2013. The preliminary data on outcomes which do not require a first checking through hospital discharge abstracts will thus be available by the end of 2014. A first publication is consequently scheduled for the second semester of 2014, and it will report also the results of the pilot nested case–control study on the subjects that accepted to participate but were excluded from the prospective cohort study because of past episodes of major diseases.

Hospital discharge abstracts are typically available in the Abruzzo region four months after the end of the year. Thus, we plan to obtain the first data on hospitalizations by May 2014, and to finish the data collection by May 2019. The final results of the study will therefore be available at the end of the first semester 2019. Eventually, in case of funds availability and approval by the Ethics Committee, the follow-up could be extended up to ten years.

The following units will participate in the project:

– Department of Medicine and Aging Sciences, University of Chieti (Coordinating unit and sponsor)

– Healthcare Professions Unit, Local Health Authority of Lanciano-Vasto-Chieti (recruitment and data collection)

– University of Turin (recruitment and data collection)

– University Sapienza of Rome (study design and analyses)

– University “Catholic of the Sacred Heart” of Rome (statistical analyses and publication support)

Other institutions and sponsors could be involved during the course of the study. In particular, additional sponsors will be actively searched.

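### Hospital outcomes 3–7 are defined by discharge codes that the study obtains only for Abruzzo residents, the stated analyses do not separate linked from unlinked participants, and asthma is in the code list but not in the outcomes

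*Protocol article*

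**What the plan says.** Under Secondary outcomes, the protocol article first states that "All outcomes will be self-reported". It then says that outcomes 3–7 will be checked using "hospital discharge abstracts through a linkage to fiscal codes (for the residents in Abruzzo only"), and that "hospitalization data will be provided by the Regional Healthcare Agency of Abruzzo". The same section defines each qualifying admission by ICD-9-CM principal-diagnosis code in the discharge abstract.

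The cohort is wider than Abruzzo. Study design and population admits any resident of Italy in the age range and says "Participants will be enrolled at various study sites within the Abruzzo and Lazio Region". Timetable, participating units and funding also lists the "University of Turin (recruitment and data collection"). Recruitment is by newspaper and internet advertisement, by contact in shops, and through some "general practitioners of the Abruzzo Section of the Italian Scientific Society of General Medicine".

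Data analysis plans Cox models for smoking-related hospitalization, with age, gender and smoking group forced in, and Kaplan-Meier analysis of hospitalization by smoking group. It names no restriction, stratification or adjustment for region or linkage status.

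On the respiratory component, the outcome text for outcomes 3–5 lists "chronic obstructive pulmonary diseases, cancer of the lung" and the other cancers, without asthma. The exclusion criteria likewise name COPD and not asthma. The code list reads "COPD or asthma" and includes the 493.xx codes.

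**The concern.** One endpoint has two ascertainment systems. For a linked Abruzzo resident, an event can be matched to a coded discharge record. For anyone else, an event is what the participant reports by telephone or website. No principal diagnosis is available for that report, a fatal admission cannot be reported by the participant, and reporting stops at dropout, which Sample size estimation expects at 20%.

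Long-term safety, measured by serious smoking-related disease requiring hospitalization, is a stated secondary aim, and the Discussion expects the data to inform guidelines and regulation. If the mix of linked and unlinked participants differs by smoking group, part of any apparent difference in admissions would reflect how events were found.

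The asthma mismatch is a separate problem. People with existing asthma are not excluded by name (the severe-allergy criterion may remove some), so their asthma admissions would count in a composite that the outcome text describes as COPD, cardiovascular disease and cancer.

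**Working it through.** **No figure to reproduce.** The article gives no event rate, event count or power for outcomes 3–7, and no distribution of smoking group by region. The calculation below is an illustration, and all its inputs are assumptions.

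**If linkage also finds unreported admissions.** Let *u* be the unlinked share in a group, *s* the fraction of true admissions captured by self-report alone, and let linkage capture be complete. With a true risk ratio of 1, the apparent ratio of group 1 to group 0 is

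RR = [(1 − u₁) + u₁s] / [(1 − u₀) + u₀s].

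- Equal shares (30% and 30%): numerator and denominator are identical, so RR = 1.00 for any *s*. Events are lost, but the ratio is not biased.
- 40% versus 20% unlinked:
  - s = 0.9: 0.96/0.98 = 0.98
  - s = 0.7: 0.88/0.94 = 0.94
  - s = 0.5: 0.80/0.90 = 0.89
- 40% versus 10% unlinked:
  - s = 0.8: 0.92/0.98 = 0.94
  - s = 0.6: 0.84/0.96 = 0.88
  - s = 0.4: 0.76/0.94 = 0.81

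If linkage captures 95% instead of all admissions, the 40% versus 20% case becomes (0.57 + 0.36)/(0.76 + 0.18) = 0.99 at s = 0.9, and (0.57 + 0.20)/(0.76 + 0.10) = 0.90 at s = 0.5. Little changes.

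**If self-report accuracy differs by group.** Equal unlinked shares then no longer protect the comparison. With 30% unlinked in both groups and capture of 0.8 in one and 0.6 in the other, RR = (0.70 + 0.24)/(0.70 + 0.18) = 0.94/0.88 = 1.07.

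**If linkage only confirms reported admissions.** False reports are then removed in Abruzzo and remain elsewhere. With 20% surplus false reports among unlinked participants and 40% versus 10% unlinked, RR = (0.60 + 0.40 × 1.2)/(0.90 + 0.10 × 1.2) = 1.08/1.02 = 1.06. The direction reverses.

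**Asthma.** This rests on the text alone. Outcomes 3–5 and the exclusions name COPD; the code list counts COPD or asthma. Outcomes 6 (cardiovascular) and 7 (cancer) are unaffected.

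**The case against.** A reader might infer that the comparison between groups is biased, or probably so, and that a group recruited more outside Abruzzo will look safer. The documents support neither step. They give no group-by-region split and assign no recruitment channel to a smoking group. With equal unlinked shares and equal reporting accuracy the ratio is 1.00. Imbalance is possible because participants choose their own smoking pattern, and because the general-practitioner channel is confined to Abruzzo while advertisements and shops are not tied to it. The direction depends on what *checked* means, and the article does not say.

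The analysis population for hospitalization is also not spelled out. The Abstract speaks of official Abruzzo discharge data, and the timetable for hospitalization data follows the Abruzzo abstracts, so an analysis of Abruzzo residents only would be compatible with the text. It should therefore not be claimed that unlinked participants contribute full person-time; ordinary censoring at dropout would limit it. Setting the analysis population is often left to a fuller document. What stands is that the article fixes a code-based definition, says that it can be verified for only part of the cohort, and describes analyses by smoking group that take no account of this.

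Nor is this the study's only long-term safety information, since side effects are collected to 60 months and the follow-up questionnaire covers diseases that did not need admission. Lastly, a reader might take the asthma codes as a further cause of regional difference. One code list applies to everyone; it would act by region only if self-reported asthma admissions went uncounted outside Abruzzo, which cannot be judged without the questionnaire.

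**Conclusion.** The point holds as a problem of ascertainment by region. Outcomes 3–7 carry a definition that cannot be applied to participants living outside Abruzzo, and the stated analyses do not separate them from linked participants. Bias between smoking groups is conditional: it needs a difference in unlinked shares or in self-report accuracy, and the documents establish neither. In the unequal-share scenarios with complete linkage capture, the apparent ratio runs from 0.98 down to 0.81 if linkage finds unreported admissions, and is about 1.06 if it only removes false reports. These figures rest wholly on assumed shares and capture rates. The asthma discrepancy is a separate and certain contradiction, limited to outcomes 3–5. The primary outcomes are untouched, so the severity is moderate.

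**What to change.** 1. Make Abruzzo residents with permission for linkage the main analysis population for outcomes 3–7. Take events from the discharge database whether or not they were self-reported, and censor at the end of linkage. This also settles what the check is for.
2. Report the whole cohort, stratified by linkage status, as a sensitivity analysis, and tabulate linkage status by smoking group so that any imbalance can be seen.
3. Reconcile outcomes 3–5 and the exclusions with the code list. Either remove 493.xx from the composite and report asthma admissions separately, or name asthma in the outcome and add a sensitivity analysis that excludes it. Both are acceptable.

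None of this needs new data. The cost is a smaller population for the main hospitalization analysis and so wider intervals, plus changes to the wording of the analysis population and the outcome definition.
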